## Abstract

**Background:**

Among the working population, unemployed, temporary agency and expired fixed-term contract workers having psychological problems are a particularly vulnerable group, at risk for sickness absence and prolonged work disability. Studies investigating the effectiveness of return-to-work (RTW) interventions on these workers, who are without an employment contract, are scarce. Therefore, a RTW intervention called ‘Brainwork’ was developed. The objective of this paper is to describe the ‘Brainwork Intervention’ and the trial design evaluating its effectiveness in reducing the duration of sick leave compared to usual care.

**Methods/Design:**

The ‘Brainwork Intervention’ is designed to assist unemployed, temporary agency and expired fixed-term contract workers who are sick-listed due to psychological problems, with their return to work. The ‘Brainwork Intervention’ uses an activating approach: in the early stage of sick leave, workers are encouraged to exercise and undertake activities aimed at regaining control and functional recovery while job coaches actively support their search for (temporary) jobs. The content of the intervention is tailored to the severity of the psychological problems and functional impairments, as well as the specific psychosocial problems encountered by the sick-listed worker.

The intervention study is designed as a quasi-randomized controlled clinical trial with a one-year follow-up and is being conducted in the Netherlands. The control group receives care as usual with minimal involvement of occupational health professionals. Outcomes are measured at baseline, and 4, 8 and 12 months after initiation of the program. The primary outcome measure is the duration of sick leave. Secondary outcome measures are: the proportion of subjects who returned to work at 8 and 12 months; the number of days of paid employment during the follow-up period; the degree of worker participation; the level of psychological complaints; and the self-efficacy for return to work. The cost-benefit analysis will be evaluated from an insurer’s perspective.

**Discussion:**

The methodological considerations of the study design are discussed. In this trial we evaluate the effectiveness of an intervention in real occupational health practice, rather than under highly controlled circumstances. The results will be published in 2015.

**Trial registration:**

Trial registration number: NTR4190

Date of registration: September 27^th^ 2013

## Background

### Unemployed and temporary agency workers and psychological problems

Workers without an employment contract, such as unemployed and temporary agency workers and workers with expired fixed-term contracts, are at a higher risk for work disability compared to the general working population, as there is no employer to return to when sick-listed or after sick leave has expired [1-7]. Workers without an employment contract represent a vulnerable group within the working population. They are characterized by a poor mental health status and a low socio-economic position [4-7]. They have less job security and are more often of non-native status, with a greater distance to the labour market, and an increased risk for work disability compared to workers with an employment contract [4,5,7]. In recent years, the number of workers without an employment contract has been growing due, in part, to the worldwide economic crisis [4,5,8-10]. As many unemployed individuals will experience psychological problems [11-14], the impact of sickness absence on public and occupational health programs/systems is important. Psychological problems are currently the leading cause of sickness absence in most high-income countries, accounting for approximately 40% of sick leave [15,16]. In the Netherlands, 40% of the sick leave of workers without an employment contract is due to psychological problems [17]. One of the primary problems these workers encounter is loss of control. In absence of an employer, regaining control by gradually returning to work is not possible. However, there are other ways to gain control and activate these workers, particularly through physical activities and volunteer work.

### The Dutch social security system

In the Netherlands, the Sickness Benefits Act provides assistance for sick-listed workers without an employment contract. The Social Security Agency (SSA) provides a sickness benefit during the first two years of sickness absence. There are no legislative mandates for these workers to be returned to their previous/last job. Therefore, the SSA is also responsible for sickness absence counselling, which is usually conducted by an insurance physician (IP).

### Study rationale

Most return-to-work (RTW) intervention research is aimed at sick-listed, currently employed workers with an employment contract. In contrast, the development of effective RTW interventions for workers without an employment contract is lagging behind [18,19]. RTW interventions need to be developed for this group because the existing RTW interventions for employed workers do not address situations in which there is no workplace to which they can return. Focusing on the ability to work is important, as working even some hours during the RTW process is an important predictor of successful RTW in this group [20]. For this purpose, and to optimize the sickness absence counselling, professionals of the SSA developed the Brainwork Intervention for workers without an employment contract, who are sick-listed due to psychological problems. The Brainwork Intervention uses an activating approach, whereby in the early stage of sick leave, the sick-listed workers are encouraged to exercise and undertake other activities concurrently with their job search.

### Objective

The objective of this paper is to describe the ‘Brainwork Intervention’ and present the design of a controlled clinical trial to study its effectiveness in reducing the duration of sick leave for sick-listed unemployed and temporary agency workers and workers with expired fixed-term contracts who have psychological problems and to compare this intervention to the usual care.

## Methods/Design

This study is being conducted as a two-armed quasi-randomized controlled clinical trial with a follow-up period of one year. To describe the design of the trial, the CONSORT statement, was followed [21,22].

### Intervention

#### Brainwork Intervention

To optimize the sickness absence counselling of sick-listed workers without an employment contract who have psychological problems, occupational health (OH) professionals of one of the front offices of the Dutch SSA developed the Brainwork Intervention. The intervention is optimized by categorizing the sick-listed workers and targeting social-medical interventions to the specific categories of workers. The core elements of the Brainwork Intervention are: (1) personal attention given by the OH professional to the sick-listed worker through face-to-face contact, within five working days after the SSA received the sick report; (2) classification of the worker based on the severity of the psychological problems, the degree of functional impairments or loss of control and estimated recovery time of the sick-listed worker by the IP (see Table 1); (3) early activation of the worker and provide structure to the worker by formulating explicit goals and timetables for recovery, the early reintegration into primary paid work and if necessary, enhancing work experience or carrying out volunteer work, and an exercise program; (4) referral of the worker to additional specific psychological and/or social interventions such as psychological treatment (e.g., dealing with coping problems or eye movement desensitization and reprocessing (EMDR) for persons with impaired trauma counselling) and debt counselling; (5) facilitating a timely internal work process for the SSA by optimizing the collaboration between the OH professionals involved (IP, vocational rehabilitation counsellor, labour expert, nurse practitioner, secretary); (6) intensive vocational counselling by the SSA; (7) counselling by a vocational rehabilitation agency.

**Table 1 Tab1:** **Brainwork category classification**

**Category 0**	**Category 1**	**Category 2**	**Category 3**
estimated recovery	estimated recovery	estimated recovery	estimated recovery
<2 weeks	<3 months	3-12 months	>12 months or unknown
Very mild problems	Mild psychological problems	Moderate- severe psychological problems include somatisation	Severe psychological problems, clinical admission or day care treatment
	***OR***	***OR***	
	Very mild problems with (severe) psychosocial problems and/or inadequate coping	Mild psychological problems with (severe) psychosocial problems and/or inadequate coping style	
	***OR***		
	Moderate- severe psychological problems with adequate coping		
No functional impairments	Functional impairments	Severe functional impairments	Severe functional impairments to inability for functioning
	(loss of control)		

The Brainwork Intervention is applicable for category 1 and 2.

The Brainwork Intervention uses an activating approach: in the early stage of sick leave, the sick-listed workers are encouraged to exercise and undertake activities aimed at regaining control and functional recovery, while job coaches actively support their search for (temporary) jobs. The tailored content of the intervention varies depending on the severity of the psychological problems and specific psychosocial problems the sick-listed worker must address. The components of the intervention include an exercise program, vocational training, gym membership and attention tailored to their mental and/or psychosocial problems. All interventions are combined with guidance from vocational rehabilitation agencies and explicit goals and timetables for recovery (see Figure 1 for an overview of the Brainwork Interventions per category). It is expected that this approach will lead to functional recovery and reduction of sick leave duration of the sick-listed worker.

**Figure 1 Fig1:**
[figure not shown]
Brainwork Intervention.

#### Rationale of the Brainwork Intervention

Hereafter, the intended mechanisms of the Brainwork Intervention components are described. (1) Face to face contact: by having a personal conversation at an early stage, the worker will feel as if his problems are taken seriously. This contact encourages the worker to make the required commitment to the intervention, which is required for achieving a positive outcome. (2) Category classification: shortly after inclusion of the worker in the program, the IP classifies the worker into a category based on the IP’s assessment of the worker’s functional impairments and estimated recovery time. A stepped care approach is used, which allows a worker with an estimated favourable recovery (estimated recovery within 3 months) to receive less intense and shorter sickness absence counselling. The classification delineates other elements of the Brainwork Intervention, namely goal-setting, increasing the efficiency of SSA work processes and worker referrals to specific interventions. The IP is asked to provide a recovery estimation of the worker based on the severity of his psychological problems and functional impairments, as well as RTW prognostic factors such as health expectations, RTW expectations and the perceived health of the worker, age, and personal factors such as education level [3,20,23]. (3) Motivate to activate: this element is designed to provide active day care for the worker. In groups with varying psychological disorders, it has been demonstrated that activation promotes recovery from mental complaints and increased functioning [24,25]. (4) Goal-setting: setting explicit goals regarding activity level of the worker and the final RTW date (or maximum duration of the sickness benefit period) is part of the Brainwork Intervention. Defining the expected recovery period will give the Brainwork participant a better perspective on his recovery, increase his sense of control, encourage a faster recovery and reduce the number of psychological complaints [26-28]. (5) Providing advice for daily structure: Brainwork participants are advised to maintain a good day structure by getting up at a specific predetermined time and planning an activity for the morning. The activity can be, for example, a visit to the gym but is not limited to exercise. This advice creates a better day-structure for the worker and may promote the recovery from mental complaints and increased functioning [24,25]. (6) Guidance to work: because work is a structuring activity, it is considered to have a positive impact on the recovery from mental complaints and increased functioning because it leads to a clear day-structure and more active day care. In addition, having a work perspective focuses the worker on improving, which has a positive effect on recovery from complaints and improved functioning. Furthermore, because there is a fast start of activities aimed at RTW and paid labour, a shorter duration of sick leave is anticipated. (7) Increased efficiency of the internal SSA work process: by optimizing the collaboration between multiple OH professionals, the prompt handling of requests regarding sickness benefit claims and quick referral to external intervention partners reduces the turnaround time and facilitates early RTW. (8) Timely referral for interventions: depending on the initial category classification of the worker, a protocol-based quick referral to external intervention partners may follow for those workers for whom a quick recovery is not expected. This method promotes a quick start of the Brainwork Intervention and is considered to have a positive effect on the mental complaints and functional recovery of the worker.

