### Study population

The population in this study consists of unemployed and temporary agency workers and workers with expired fixed-term contracts, who live in the eastern, south-western or southern part of the Netherlands and when sick-listed are the responsibility of the three participating front offices of the Dutch SSA. The inclusion criteria are: (1) being an unemployed or temporary agency worker or worker with an expired fixed-term contract; (2) between 18 and 64 years of age; (3) sick-listed and not expected to RTW within two weeks after reporting sick or contact with the vocational rehabilitation counsellor of the SSA; (4) having psychological problems/complaints as the main reason for a sickness benefit claim; and (5) adequate command of the Dutch language. The exclusion criteria are: (1) recent pregnancy or up to three months after delivery; (2) substance addiction (alcohol, drugs and medicines) as the main reason for a sickness benefit claim; (3) having a severe psychiatric disorder with an expected recovery of more than one year (e.g., hospitalization or day treatment).

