### Sample size and power analysis

A power analysis was performed to calculate the required number of participants in this study. The mean and standard deviations of the duration of sick leave of all sick-listed workers without an employment contract having psychological problems who registered at the SSA in 2011 were taken as a starting point. Because there are no data available from previous studies on the expected differences, we only calculated how many participants are needed to display any differences in duration of sick leave. The power analysis using program nQuery Advisor showed that 144 participants are needed per group (288 total) to detect a mean difference in duration of sick leave of 40 days. Therefore, we decided to include 300 participants for this study.

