### Data analysis

All statistical analyses will be performed at worker’s level according to the intention-to-treat principle. To check the success of the quasi randomisation procedure similarities in the descriptive statistics will be determined, comparing the baseline measurements of both groups. If necessary, the main analyses will be adjusted for prognostic dissimilarities. For those aspects of the protocol which were fixed for all participants, such as personal attention given by the OH professional to the sick-listed worker through face-to-face contact within five working days after the SSA received the sick report, or timely referral of the worker to the external intervention partner, the protocol deviations will be analyzed. To assess the presence of bias due to protocol deviations, the results of the intention-to-treat analyses will be compared to per-protocol analyses.

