#### Effect evaluation

To assess the effectiveness of the Brainwork Intervention for the primary outcome, a Linear Mixed Models (LMM) analysis of the differences between the average sick leave duration (in days) in the intervention and control group will be performed. Therefore, a model with group as fixed factor and the vocational rehabilitation counsellor of the SSA at a primary hierarchical level and the participants at a secondary hierarchical level (where appropriate) will be built. For all participants who have not returned to work after 1 year of follow-up, the value of 365 days of sickness absence will be imputed.

For the secondary outcomes, excepting costs and benefits, LMM analysis for continuous outcomes and Generalized Linear Mixed Models analysis for dichotomous/ordinal outcomes will be performed. Therefore, a model with group as fixed factor and the vocational rehabilitation counsellor of the SSA at a primary hierarchical level and the participants at a secondary hierarchical level (where appropriate) will be built. In the case of differences in the ratios between the types of workers (unemployed and temporary agency versus expired fixed-term contract) due to attrition, a correction for the differences will be performed by including type of worker as a covariate in the analysis.

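### Age, which the protocol itself calls prognostic and must know for every worker, enters the primary model only if the arms are judged to differ; this gives up some precision and leaves the model open until the data are seen

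*Protocol article*

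**What the plan says.** Three parts of the protocol article bear on this.

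- **The analysis rule.** Under Data analysis, the success of the quasi-randomisation is checked: "similarities in the descriptive statistics will be determined, comparing the baseline measurements of both groups". Then: "If necessary, the main analyses will be adjusted for prognostic dissimilarities". No covariate is named, and nothing says how large a difference makes adjustment necessary.
- **The model.** Effect evaluation specifies "a model with group as fixed factor and the vocational rehabilitation counsellor of the SSA at a primary hierarchical level", with participants at the next level. Group is the only fixed term. The one covariate named anywhere is type of worker, and it is conditional too: the correction by "including type of worker as a covariate in the analysis" applies only if attrition changes the mix of worker types.
- **The premise about age.** Under Rationale of the Brainwork Intervention, the physician's recovery estimate draws on "RTW prognostic factors such as health expectations, RTW expectations and the perceived health of the worker, age, and personal factors such as education level". Under Study population, a worker must be "between 18 and 64 years of age" to be included.

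The size of the trial comes from Sample size and power analysis: "144 participants are needed per group (288 total) to detect a mean difference in duration of sick leave of 40 days", and hence "we decided to include 300 participants for this study".

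**The concern.** A baseline covariate improves a comparison of means to the extent that it predicts the outcome. Whether the arms happen to differ on it in the sample is a different matter. A rule that waits for a visible difference therefore leaves a prognostic factor out of most analyses in which it would have narrowed the confidence interval.

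Two further costs follow. First, an imbalance large enough to matter but not judged a dissimilarity stays in the estimate. Second, with no criterion and no list of covariates, the primary model is settled only after the data have been looked at. Both weigh somewhat more here than in a concealed randomised trial, because allocation runs in alternating fives and nobody delivering or receiving the intervention is blinded.

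Age is the plain case. The protocol calls it prognostic, it is fixed before allocation, and it does not depend on the posted questionnaire. That it is available as an analysis variable is an inference from the eligibility criterion, but a safe one.

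**Working it through.** **Inputs.** From the protocol: a 40-day difference, 144 per group, 300 in total. Assumed, because the article does not give them: two-sided 5%, 80% power (90% as an alternative), 150 per arm from the alternating allocation, and the share of variance in sick leave duration explained by age (R²), taken as 1% to 10%.

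**Step 1: the plan's own figure.** It cannot be confirmed or refuted without SD, alpha and power. It can be inverted:

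SD = 40 × √(144/2) / (1.960 + 0.842) ≈ 121 days at 80% power.

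At 90% power the same formula gives about 105 days. Putting 121 days back in returns 144 per group.

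**Step 2: power with and without age.** The unadjusted standard error is 121 × √(2/150) = 13.97 days. With age in the model it is 13.97 × √(1 − R²). Power = Φ(40/SE − 1.960). The equivalent gain in participants is 300/(1 − R²) − 300.

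| R² of age (assumed) | SE (days) | Power | Equivalent extra participants |
|---|---|---|---|
| not adjusted | 13.97 | 81.7% | – |
| 1% | 13.90 | 82.05% | 3 |
| 2% | 13.83 | 82.4% | 6 |
| 5% | 13.62 | 83.6% | 16 |
| 10% | 13.26 | 85.5% | 33 |

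The gain is about 0.4 to 3.8 percentage points. With an SD of 104.5 days (the 90% design), power goes from 91.2% to between 91.5% and 93.75% over the same range.

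**Step 3: how much of the gain the conditional rule keeps.** The protocol gives no trigger, so a baseline difference at p < 0.05 was assumed. Simulation used 40,000 trials per setting, SD 121 days and 150 per arm, without clustering by counsellor and without the 365-day cap. Here r is the correlation of age with duration. Age was adjusted for in about 5% of trials.

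| r (R²) | Power: never | Power: only if p < 0.05 | Power: always | Type I error: only if p < 0.05 |
|---|---|---|---|---|
| 0.1 (1%) | 81.5% | 81.5% | 81.8% | 5.08% |
| 0.2 (4%) | 81.2% | 81.4% | 82.8% | 5.05% |
| 0.3 (9%) | 81.4% | 81.8% | 84.7% | 4.80% |

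The conditional rule keeps almost none of the gain. Its overall type I error is not raised. At r = 0.5, beyond the range above, it is 4.32%.

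**Step 4: samples with a moderate imbalance left unadjusted.** Suppose the arms differ in age by z standard errors. Under no effect, the unadjusted test statistic is then normal with mean r·z and variance 1 − r², and the bias is r·z × 13.97 days.

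- For z = 1.5 to 1.9 and R² = 5% (r = 0.224): bias 4.7 to 5.9 days, conditional error 5.7% to 6.5%.
- For the same z and R² = 10% (r = 0.316): bias 6.6 to 8.4 days, conditional error 6.4% to 7.9%.
- Under chance allocation, an imbalance of that size occurs in 2 × [Φ(1.9) − Φ(1.5)] = 7.6% of samples.
- At z = 0 the conditional error is 4.4% (R² = 5%) or 3.9% (R² = 10%).
- Averaged over every imbalance below 1.96 standard errors, it is 4.9% and 4.7%.

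**Step 5: discretion.** If the open wording allowed the more favourable of the adjusted and unadjusted results to be reported, simulated type I error would be 5.5%, 6.1% and 6.5% at r = 0.1, 0.2 and 0.3. This is an upper bound on misuse. The protocol does not describe such a procedure.

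**The case against.** The strongest reply is that this is a small matter of efficiency. The article gives no association between age and duration, age is one of several factors listed, and the sentence naming it describes a clinical estimate within the intervention, not an analysis. The calculation leaves out the counsellor level and the 365-day cap. All of this stands, and it is why the gain is given as a range with a low bottom end.

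A reader might infer that the primary test exceeds its nominal error rate. The document does not support that. The rates of 5.7% to 7.9% belong to a slice of about 7.6% of samples, and only under a 5% check that the protocol never states. Under a fixed trigger the overall rate is at or slightly below nominal. A reader might also infer that covariates would be picked by their effect on the result. The stated trigger is a comparison of baseline measurements, so the fair criticism is only that it has no criterion and no list.

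It can also be said that naming covariates is commonly left to an analysis plan. That would hold if the article were silent. It states a conditional rule, and a later plan that included age unconditionally would have to depart from it.

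Finally, type of worker, the factor used for pre-stratification, is also only a conditional covariate. That is true, but it does not weaken the case for age.

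**Conclusion.** The point holds as a modest, nearly cost-free improvement. The adjustment rule under Data analysis, read with the model under Effect evaluation, leaves out a factor the protocol itself regards as prognostic unless an undefined dissimilarity appears. Under an SD of about 121 days, two-sided 5% and 150 per arm, this forgoes roughly 0.4 to 4 points of power if age explains 1% to 10% of the variance. That share is an assumption.

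The remaining harm is a possible bias of about 5 to 8 days, at R² of 5% to 10%, in the minority of samples where a moderate age imbalance goes unadjusted, together with a primary model that is not fixed in advance. Inflated overall type I error is not part of the conclusion. Nor is any error in the sample size of 144 per group, which cannot be checked from what is printed.

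**What to change.** In Data analysis and Effect evaluation, state that age at the sick report is a fixed covariate in the primary model whether or not the groups differ at baseline. Keep the provision for other observed prognostic dissimilarities, but as a sensitivity analysis alongside the prespecified primary result. It should not be dropped: with open, predictable allocation in fives, imbalance need not be due to chance, and this is the protocol's only general safeguard against it.

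The cost is a sentence or two and one degree of freedom, with no extra participants and no data beyond what eligibility already requires. The change must be made before outcome data are examined. If age is also added to the mixed models for the dichotomous and ordinal secondary outcomes, their odds ratios become conditional on age, and the report should say so.
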